#### 2.10.1. Primary Outcomes

Primary outcomes will be executive function and fall risk. The executive function will be measured using the Trail Making Test (TMT) [38]. This test is widely used to assess executive abilities in stroke survivors [39]. Participants will be instructed to draw lines connecting numbers in numerical order (TMT Part A) and numbers and letters in an alternating ascending sequence (TMT Part B) as quickly and accurately as possible [38]. The score for each part represents the time required to complete the task. Besides the direct scores, the B–A difference score will represent an executive function [38].

Fall risk will be assessed using the Timed Up and Go (TUG) test [40]. The TUG test has been demonstrated to be valid and to identify the risk of falling in community-dwelling older adults as well as in stroke patients [40]. Participants will be instructed to stand up from a chair, walk 3 m at their maximum safe pace, turn around, return to the chair, and sit down. Participants will be allowed to wear their usual shoes and use their assistive devices and/or orthoses if needed. The average time to complete the test in 2 trials will be recorded.

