### 2.5. Sample Size

The sample size was calculated using G*Power version 3.1.9.2 based on outcome measures. Effect sizes were derived from previous studies, which reported values of 0.46 for executive function [34], 0.57 for fall risk [35], and 0.37 for gait speed [36,37]. With a power of 0.80 and an alpha level of 0.05, sample sizes of 30, 20, and 46 will be required to detect a change in executive function, fall risk, and gait speed respectively. Accordingly, a total sample size of 46 participants is considered sufficient to detect changes in outcome measures. To accommodate a 10 percent dropout rate, a total of 52 participants (26 per group) will be enrolled in the study. However, the appropriate sample size will be recalculated using data from our preliminary study.

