
### 2.11. Statistical Analyses

Descriptive statistics will be used to summarize the demographic data and baseline characteristics of each group. Data normality will be assessed using the Kolmogorov–Smirnov test. Homogeneity of variances will be evaluated using Levene’s test. Independent-samples *t*-tests and chi-square tests will be used to compare demographic characteristics between the intervention and control groups. The primary analysis will be conducted using a two-way mixed-model ANOVA to examine differences in outcome measures between groups across two assessment time points (baseline and 12 weeks). The Bonferroni correction will be used for the post hoc analysis. In case of baseline imbalances, an analysis of covariance (ANCOVA) will be conducted to compare post-intervention outcome measures between groups, with baseline scores and time since stroke included as covariates to control for potential confounding effects. However, if data are not normally distributed, appropriate nonparametric methods will be considered. The primary comparative analyses will follow the intention-to-treat principle. Missing data will be handled using multiple imputation by chained equations, generating five imputed datasets. The imputation model will include all outcome variables, baseline scores, and relevant covariates. Additionally, a per-protocol analysis will be performed for the primary outcomes to evaluate the intervention effects among participants who attended at least 80% of the sessions. Statistical significance will be set at *p* < 0.05.

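### Two separate primary outcomes are each tested at p < 0.05 with no rule for combining them, so the chance of at least one false positive primary is about 9% to 10% if either can carry the claim

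*Protocol article*

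**What the plan says.** Section 2.10.1 of the protocol article: "Primary outcomes will be executive function and fall risk". Fall risk is measured by one score, the mean TUG time over two trials. Executive function is measured by the TMT. For its two parts, "The score for each part represents the time required to complete the task", and then "Besides the direct scores, the B–A difference score will represent an executive function".

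Section 2.11: "The primary analysis will be conducted using a two-way mixed-model ANOVA to examine differences in outcome measures between groups across two assessment time points". On multiplicity it says only "The Bonferroni correction will be used for the post hoc analysis". The section closes with "Statistical significance will be set at" p < 0.05, without distinguishing primary from other outcomes.

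Section 2.5: "With a power of 0.80 and an alpha level of 0.05, sample sizes of 30, 20, and 46 will be required" for executive function, fall risk and gait speed in turn. Each primary is therefore sized at the full alpha.

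**The concern.** Two primary outcomes give two chances of a positive primary result. If either is enough to call the programme effective, the 5% error rate attached to each test is not the error rate of the claim.

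The Bonferroni sentence does not close this gap. With two groups and two time points, post hoc tests are pairwise comparisons of cells within one outcome. They do nothing about error across TMT and TUG.

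The executive-function endpoint adds a second, smaller problem. The TMT yields three scores, and the text introduces B–A alongside the two direct times without saying that only B–A is primary. If that stays open until the data are in, the score to be reported as primary could be chosen after the results are known.

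**Working it through.** **Inputs from the protocol article.** Two primary outcomes (2.10.1); 0.05 per test (2.11, 2.5); effect sizes 0.46 for executive function, 0.57 for fall risk and 0.37 for gait speed; power 0.80; N of 30, 20 and 46; 10% dropout; 52 enrolled (2.5).

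**Inputs assumed.** The documents give no correlation between TMT and TUG, no correlation between Parts A and B, no ratio of their SDs, no effect-size metric and no correlation between repeated measurements. Each is varied or flagged below.

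**1. The plan's own sample sizes.** Treat the effect sizes as Cohen's f in a repeated-measures ANOVA, between-groups effect, 2 groups, m = 2 measurements, correlation ρ = 0.5. The noncentrality is λ = f²·N·m / (1 + (m − 1)ρ) = f²·N·2/1.5, with 1 and N − 2 degrees of freedom.
- Executive function: f = 0.46, N = 30, λ = 0.2116 × 30 × 2/1.5 = 8.46, power 0.802. Required N is 30, as stated.
- Fall risk: f = 0.57, N = 20, λ = 0.3249 × 20 × 2/1.5 = 8.66, power 0.795. The smallest even N reaching 0.80 is 22, against 20 stated.
- Gait speed: f = 0.37, N = 46, λ = 0.1369 × 46 × 2/1.5 = 8.40, power 0.809. Required N is 46, as stated.
- Dropout: 46/0.90 = 51.1, which gives 52 in two equal groups, as stated.

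This reading approximately reproduces the plan. Reading the values as standardised mean differences in a two-sided t test gives 152, 100 and 232. A one-way ANOVA with f gives 40, 28 and 60, and the group-by-time interaction with f and ρ = 0.5 gives 12, 10 and 18. None of these fits.

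**2. Error over two primary tests (B–A and TUG), either one sufficient.**
- Independent: 1 − 0.95² = 0.0975.
- Test statistics correlated 0.3: 0.095.
- Test statistics correlated 0.5: 0.091.

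**3. Error if all three TMT scores and TUG counted as primary.** B–A is computed from A and B, so the independence figure of 1 − 0.95⁴ = 0.185 cannot apply. Simulating null test statistics with the SD of B twice that of A:

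| Correlation A, B | TUG–TMT correlation 0 | 0.3 | 0.5 |
|---|---|---|---|
| 0.5 | 15.7% | 15.4% | 14.7% |
| 0.7 | 15.0% | 14.7% | 14.0% |

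Over wider assumptions (A–B correlation 0.3 to 0.8, SD ratio 1.5 to 3) the range is 12.6% to 16.2%.

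**4. Cost of splitting alpha over the two primaries.** The formula of step 1, at alpha 0.025:
- Executive function needs 38. Power at N = 46 goes from 0.94 at alpha 0.05 to 0.90 at 0.025.
- Fall risk needs 26. Power at N = 46 goes from 0.99 to 0.98.

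Both requirements are below 46. Gait speed, which set the 46, is a secondary outcome (2.10.2), so its requirement is unchanged.

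**The case against.** The strongest reply is that the inflation depends on a success rule that the article does not state. Nothing requires both primaries to succeed, but nothing says that one suffices. If both had to be positive there would be no inflation. If each domain gets its own separate conclusion, each conclusion carries 5%, and whether to adjust across them is debated. A full protocol or analysis plan might settle this. That is a fair limit on the size of the finding, and the 9% to 10% is stated conditionally for that reason. It does not remove the point. The article is not merely silent: it fixes the threshold, says where correction applies, and sizes each primary at full alpha. Followed as written, it leaves the two primaries uncorrected.

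A reader might also infer that there are four primary p-values and an error rate of about 15%. The documents do not support that as the main reading. Only of B–A is it said that the "difference score will represent an executive function", and nowhere is Part A or Part B time called a primary endpoint that could carry a claim alone. The 15% also rests on correlations and an SD ratio that the article does not give. What stands is that the reference to the direct scores leaves the possibility open.

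Finally, the effect-size metric and the correlation behind section 2.5 are not stated, and the same section says the sample size will be recalculated from preliminary data. The statement that no extra participants are needed is therefore conditional.

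**Conclusion.** The concern holds in this form. The plan tests two separate primary outcomes at 0.05 each, with no correction across them and no rule on whether one or both must succeed. If either can support the effectiveness claim, the chance of at least one false positive primary is 9.1% to 9.75%, for test correlations from 0.5 down to 0. A figure near 15% applies only if TMT-A, TMT-B and B–A are all treated as primary, with an assumed A–B correlation of 0.5 to 0.7 and the SD of B twice that of A. It marks how far the loose wording could stretch, not what the plan states.

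**What to change.** In section 2.10.1, name TMT B–A as the single executive-function primary endpoint, which follows the section's own statement of what B–A represents. List TMT-A and TMT-B times as secondary, and name TUG time as the fall-risk primary endpoint.

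In section 2.11, state that the two primaries are tested by Holm at familywise 0.05: the smaller p-value against 0.025 and, only if that is significant, the larger against 0.05. Leave the existing secondary outcomes as secondary, because this problem gives no reason to relabel them.

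The text change is short, but the trial is registered and recruitment began in February 2026 (section 2.2). It should therefore be made as a dated amendment, with the registration brought into line, before any outcome data are examined. The planned sample-size recalculation should use the alpha that follows from this rule.

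The statistical cost is a small loss of power per primary: 0.94 to 0.90 for executive function and 0.99 to 0.98 for fall risk at N = 46, taking 0.025 as the worst case under Holm. If the effect sizes are Cohen's f with correlation 0.5, no extra participants are needed.

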#### 2.10.2. Secondary Outcomes

Secondary outcome measures will include global cognitive function, memory, attention, motor function, gait speed, balance, limits of stability, muscle power, weight distribution, body composition, enjoyment, and adherence. Global cognitive function will be assessed using the Montreal Cognitive Assessment (MoCA) [41]. The MoCA is a reliable tool for assessing global cognition in stroke survivors [42]. The maximum possible score is 30 points. To adjust for educational level, one additional point will be added for participants with ≤12 years of education. Memory and attention will be assessed using the Digit Span Test [43]. Participants will be asked to repeat sequences of digits presented verbally either in the same order (forward) or in reverse order (backward). The number of correctly recalled sequences for each condition will be recorded [43].

Motor function, gait speed, balance and limits of stability, muscle power, and weight distribution will be assessed using the Motor Assessment Scale (MAS) [44], 10-Meter Walk test (10MWT) [45], the Modified Functional Reach Test (MFRT) [46,47], 5 times sit-to-stand test (5TSTS) [48], and the Stance Symmetry Test (SST) [49], respectively. For the MAS test, participants will be asked to perform 8 items of functional tasks: supine to side lying, supine to sitting, balance sitting, sitting to standing, walking, upper arm function, hand movement, and advanced hand activities. Each item is scored on a 7-point scale (0–6; 0 = no function to 6 = normal function), based on a person’s ability to perform specific tasks. Participants will perform each task three times and the best performance will be recorded. For the 10MWT, participants will be instructed to complete a 10 m walk at a self-selected speed with or without walking aids [45]. An acceleration distance of 2 m and a deceleration distance of 2 m will set up at the beginning and the rear end. The time will be recorded by digital stopwatch for the middle 10 m distance. Measurements will be determined twice. The speed will be calculated by dividing the distance by time (m/s). Dynamic balance and limits of stability while sitting will be measured by MFRT [46]. Participants will be sitting on a standard chair with their feet shoulder-width apart, flat on the floor, hips and knees at 90° flexion with the non-paretic side closest to the wall. The participant will be instructed to reach as far as possible with the arm horizontal while maintaining balance. The location of the fifth finger at the beginning and the end of the reach will be recorded. MFRT will consist of three conditions including forward reach while sitting with the unaffected side near the wall, lateral reach to the right while sitting with the back to the wall, and lateral reach to the left while sitting with the back to the wall. Each participant will perform a total of five trials per condition. The first two trials will be used for familiarization, and the mean of the final three trials will be used for analysis [46,47]. As for muscle power, participants will be instructed to perform five sit-to-stand repetitions as quickly as possible. The time required to complete the task will be recorded [48]. Weight distribution will be measured using the SST. This test assesses the distribution of weight between both legs. Participants will be instructed to stand with each foot on a separate weighing scale, with the distance between the feet set at 11% of the participant’s height. They will be asked to stand as still as possible for 30 s. The assessors will record the weight borne by each leg at 25 s. Each participant will complete three trials, and the results will be averaged. The symmetry ratio will be calculated as the average weight bearing through the affected leg divided by the average weight bearing through the non-affected leg [49]. Furthermore, minimum detectable difference (MDD) values for the MFRT, 5TSTS, and SST will be used to aid the interpretation of clinical significance. Body fat percentage and fat mass will be measured using a body fat composition monitor with an accuracy of 0.1 kg and 0.1%, respectively [50,51]. In addition, the Physical Activity Enjoyment Scale (PACES) will be used to assess participants’ enjoyment during the intervention [52]. PACES consists of eight items rated on a 7-point Likert scale from 1 (strongly disagree) to 7 (strongly agree). The overall enjoyment score will be derived from the sum of all item scores. Furthermore, adherence to the intervention will be recorded and calculated as the percentage of attended physical–cognitive training sessions using (n/36) × 100.

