### 2.3. Settings and Participants

The intervention will be delivered in a home-based format at each participant’s home. Participants will be included if they have been diagnosed with ischemic or hemorrhagic stroke at least 6 months before enrolment [31], are aged between 20 and 80 years [31], are able to walk at least 10 m with or without assistive devices [32], are able to perform sit-to-stand safely with or without assistive devices, can see the screen of a tablet or notebook computer at a distance of at least 60 cm [33], have a stable medical condition and are able to follow study instructions [32], and are frequent users of a mobile phone, tablet, or notebook computer. Participants will be excluded from the study if they have medical conditions or complications that would be unsafe to exercise [31], have neglect, impaired communication, or uncorrected visual problems [32], or have severe spasticity of the upper or lower extremities (Modified Ashworth Scale ≥ 3) [31,32].

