### 2.8. Interventions

#### 2.8.1. Web-Based Physical–Cognitive Telerehabilitation Exergaming

Participants will perform a physical–cognitive exergame via ExerbrainCMU web-based platform at home setting for 60 min/session, 3 sessions/week for 12 weeks. The program will consist of warm-up, physical–cognitive training, and followed by cool-down. The physical–cognitive exergame will consist of trunk exercises, upper- and lower-extremity exercises, exercises using Proprioceptive Neuromuscular Facilitation (PNF) patterns, balance exercises, aerobic exercises, sit-to-stand training, and side-walking exercises, combined with cognitive training targeting executive function, attention, memory, visuospatial ability, and dual-task performance. In general, physical–cognitive exergames will mostly be performed in a sitting position. Task difficulty will be progressively increased by manipulating movement complexity, speed, and directional demands, while cognitive load will be adjusted by varying cognitive complexity, the number of stimuli, task conditions, attentional demand, and memory load. The intervention will comprise three difficulty levels: easy (weeks 1–4), medium (weeks 5–8), and hard (weeks 9–12). Participants scoring below 80% across all games will be required to repeat the current level until the 80% passing criterion is met before progressing to the next level. Instructional materials, including basic instructions and training videos, will be provided to ensure correct and safe execution of the intervention. A summary of the intervention is presented in Figure 2 and Table S2 (Supplementary Materials).

Telerehabilitation will be conducted using the ExerbrainCMU web-based platform. Participants will engage in exercise training at home or in remote areas via simultaneous video conferencing, accompanied by a physiotherapist. The telerehabilitation system consists of a main monitoring controller for physiotherapists, a network data system, and connected end-users who are stroke patients. The main monitoring controller enables therapists to monitor exercise accuracy and safety at weeks 2, 4, 8, 10, and 12. Family members or caregivers may stand beside participants if there are safety concerns.

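### Lateral seated reach is scored only from finger travel and split by right and left, so reach toward the paretic side is unscorable for some eligible people and mixes arm with trunk movement in others

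*Protocol article*

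**What the plan says.** Section 2.10.2 of the protocol article gives the MFRT this role: "Dynamic balance and limits of stability while sitting will be measured by MFRT [46". The instruction is "The participant will be instructed to reach as far as possible with the arm horizontal while maintaining balance", and the score comes from one landmark: "The location of the fifth finger at the beginning and the end of the reach will be recorded".

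There are three conditions. Forward reach is set up with the unaffected side near the wall. The other two are one per side, done with a wall behind the participant: "lateral reach to the right while sitting with the back to the wall, and lateral reach to the left while sitting with the back to". All participants do all three: "Each participant will perform a total of five trials per condition", with the last three averaged. Minimum detectable difference (MDD) values will help to interpret MFRT change.

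Section 2.3 requires the ability to walk 10 m and to stand up from sitting. Its only limb-specific exclusion is for people who "have severe spasticity of the upper or lower extremities (Modified Ashworth Scale ≥ 3"). Section 2.10.2 also scores upper arm function on the Motor Assessment Scale (MAS) from 0, meaning no function.

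The intervention in section 2.8.1 includes "upper- and lower-extremity exercises, exercises using Proprioceptive Neuromuscular Facilitation (PNF) patterns". Controls receive no added intervention (section 2.8.2). Section 2.11 handles missing data by multiple imputation with five datasets: "The imputation model will include all outcome variables, baseline scores, and relevant covariates".

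**The concern.** Two things go wrong in the lateral condition toward the paretic side.

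First, the score needs an arm that can be held horizontal, and nothing at entry ensures this. A weak or flaccid arm is not an exclusion. Such a participant would have no paretic-side score, typically at both visits, because of impairment and not because of a missed visit. Imputation would then supply a reach modelled on people who can raise the arm. A participant who regains arm elevation would move from unscored to scored, so whether a score exists could depend on treatment.

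Second, finger travel is trunk displacement plus any arm extension added during the reach. The arm is trained in one group only, so some of a between-group difference labelled as balance could be arm function, in favour of the intervention.

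Defining the variables as right and left compounds both problems. Each variable then contains paretic reach for some participants and non-paretic reach for the others, so neither has a clear clinical meaning.

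**Working it through.** **Reading the sections together.** The plan states no figure for this point, so there is none to reproduce.

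- Conditions: only forward reach is set up around the unaffected side. Everyone reaches both right and left, so anyone with a paretic side has one lateral condition toward it.
- Reaching arm: not named for the lateral conditions. With the back to the wall and the arm horizontal, the natural reading is the arm on the side of the reach. This is an inference.
- Landmark: the fifth finger only. No alternative score is given for a participant who cannot raise the arm.
- Eligibility: no arm-function criterion, so such a participant can be enrolled.

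**How many scores could be lost.** The article gives no share p unable to hold the paretic arm horizontal. I assume 10% to 50%, with paretic side split evenly. Paretic-side scores lost = 52p; loss per right or left condition = 52p/2.

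| p | No paretic-side score (of 52) | Lost per right or left condition |
|---|---|---|
| 10% | 5.2 | 2.6 (5%) |
| 20% | 10.4 | 5.2 (10%) |
| 30% | 15.6 | 7.8 (15%) |
| 50% | 26 | 13 (25%) |

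For a right or left variable the variance of the estimate rises by 1/(1 − p/2): 1.11-fold at p = 20% and 1.33-fold at p = 50%. For a variable defined by paretic side it would rise by 1/(1 − p), that is 1.25-fold and 2-fold, but the article defines no such variable.

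**Chance that an arm gain alone is significant.** Assumed inputs: trunk displacement unchanged; a gain g of 1 to 3 cm in arm extension during the reach; SD of change s of 4 to 6 cm; 23 per arm (the 46 of section 2.5, equally split); two-sided t-test at 0.05, noncentral t with noncentrality (mean gain/s) × √(n/2), where n is the number per arm.

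- (a) Every intervention participant reaches with a scorable paretic arm, mean gain = g. For g = 1, s = 6: (1/6) × √11.5 = 0.57, chance 8.6%. For g = 3, s = 4: (3/4) × √11.5 = 2.54, chance 70.1%.
- (b) A right or left condition as defined: about half reach with the paretic arm, so mean gain = g/2. Noncentrality 0.28 to 1.27, chance about 6% to 24%.
- (c) As (b), with unscorable participants removed: n = 23(1 − p/2), mean gain = g × 0.5(1 − p)/(1 − p/2).
  - p = 20%: n = 20.7, mean gain 0.44g, chance about 6% to 18%.
  - p = 50%: n = 17.25, mean gain 0.33g, chance about 5% to 11%.

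Cases (b) and (c) match the variables in the article; case (a) does not. Together they give about 5% to 24%.

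**The case against.** The strongest reply is that this is a gap in description. The MFRT is an established test taken from cited sources. Those sources or the full protocol may say which arm is used and how to score someone who cannot raise it, and an article commonly leaves such detail out. The sentences on the horizontal arm and the finger follow directly on a set-up with the non-paretic side nearest the wall, so applying them to lateral reach with the paretic arm is an inference. That caution stands. It does not remove the point, because the article does state the landmark, the arm position, the right and left conditions and that every participant does them. Followed as written, those rules give the problem described.

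Other parts of the reply also stand and limit the point:

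- The score is end minus start position of the same finger. An improvement already present at the start of the reach cancels; only extension added during the reach counts.
- The MAS has a sitting-balance item, so the MFRT is not the only assessment that touches seated balance, although the article assigns the MAS to motor function.
- The imputation model contains all outcomes, so MAS and the other reach conditions do inform it. Even so, the imputed value is a finger reach for someone who could not perform one.
- A scale that starts at 0 does not show that people with no arm function will be enrolled.

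A reader might infer that arm gain could produce a false balance result with a chance as high as 70%, or that the trial's balance conclusion as a whole is biased. The documents do not support either. The 70% requires every intervention participant to reach with a scorable paretic arm, which no defined variable has. Forward reach and non-paretic lateral reach do not depend on the paretic arm.

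**Conclusion.** The point holds within limits. As written, and taking the reaching arm to be the one on the side of the reach, paretic-side reach has no score for eligible people who cannot raise that arm. Its absence is handled by imputation, and each right or left variable mixes two different measurements. Where a score exists, any contamination by arm gain runs in favour of the intervention.

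The size is unknown. The share affected, the arm gain and the SD of change are all assumptions; under them the chance of a significant right or left result from arm gain alone is about 5% to 24%.

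The scope is one direction of one secondary instrument. Forward reach, the primary outcomes (Trail Making Test and Timed Up and Go) and the sample size are not affected. It is still worth correcting, since recruitment began in February 2026 and the main changes need no new measurements.

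**What to change.** 1. Name the reaching arm for each MFRT condition.
2. Recode lateral reach as paretic or non-paretic, using the paretic side already collected under section 2.4.
3. Base the MFRT balance conclusion on forward reach and non-paretic lateral reach. Report paretic-side finger reach separately, described as a measure that mixes arm and trunk. The separation matters because recoding removes the dilution by non-paretic reach, so an arm gain shows more strongly in the paretic-side variable.
4. Do not impute finger reach for participants recorded as unable to raise the arm. Report their number by arm and visit.

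Items 2 and 3 change only the analysis wording. Items 1 and 4 need a line in the assessor instructions and a recorded reason when a reach cannot be scored. The cost is that stability toward the paretic side, which is of clinical interest, carries less weight.

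Recording displacement of the acromion on the paretic side is optional. It would give a trunk-based score without arm elevation, but participants already assessed have no baseline for it and finger-based MDD values would not apply.

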### 2.4. Participant Characteristics

Participant characteristics including age, body mass index, gender, and education level will be recorded. Medical information regarding stroke characteristics, including stroke type, paretic side, and time since stroke onset will also be collected.

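### Lateral reach is defined by right and left rather than by paretic side, so each lateral measure averages weak-side and strong-side reach and loses power if the effect differs by side

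*Protocol article*

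**What the plan says.** Section 2.10.2 of the Protocol article lists three MFRT conditions. The first is "forward reach while sitting with the unaffected side near the wall". The other two are "lateral reach to the right while sitting with the back to the wall, and lateral reach to the left". Each condition has five trials, of which the first two are for familiarization, and "the mean of the final three trials will be used for analysis".

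The stance symmetry ratio, described in the same section, is "average weight bearing through the affected leg divided by the average weight bearing through the non-affected leg".

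Section 2.4 states that "stroke type, paretic side, and time since stroke onset will also be collected". Section 2.3 requires that participants were "diagnosed with ischemic or hemorrhagic stroke at least 6 months before enrolment" and sets no restriction on which side is paretic.

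Section 2.11 analyses outcomes by a two-way mixed ANOVA of group and time. If there is baseline imbalance, it uses an ANCOVA with baseline score and time since stroke as covariates. Paretic side appears in neither model, and nothing in the article links right or left reach to paretic or non-paretic side.

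**The concern.** Forward reach and stance symmetry are anchored to the affected side; lateral reach is anchored to the anatomical side. In a sample that mixes left and right hemiparesis, reach to the right goes toward the weak side for some participants and toward the strong side for others. Reach to the left is the mirror image.

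A between-group difference in right reach is then an average of two effects, weighted by how many participants are paretic on the right. If the programme improves reach in one direction more than the other, both lateral measures show a blend and neither isolates the direction that responds. Two of the three conditions of the balance and limits-of-stability outcome are concerned. Section 2.10.2 also intends to read the MFRT against minimum detectable differences, which is simpler when a measure means the same direction in every participant.

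**Working it through.** **Inputs from the Protocol article.** 52 enrolled, 26 per arm, 10% dropout (2.5); significance level 0.05 (2.5, 2.11); group-by-time mixed ANOVA at two time points (2.11). Section 2.5 sizes the trial on other outcomes, so there is no MFRT figure to reproduce. The enrolment arithmetic holds: 46/(1 − 0.10) = 51.1, giving 52 in two equal groups, or 23 evaluable per arm after dropout.

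**Inputs that are assumptions.** Effect of 0.6 SD toward the paretic side; effect of k × 0.6 SD toward the other side; baseline-to-12-week correlation ρ = 0.7; share p = 0.5 paretic on the right; two-sided test.

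**Step 1: paretic coding.** With two time points, the group-by-time test is a t-test on change.
- Variance of change = 2(1 − ρ) = 2 × 0.3 = 0.6, so SD = 0.775.
- Standardised effect = 0.6/0.775 = 0.775.
- Noncentrality = 0.775 × √(26/2) = 2.79 on 50 degrees of freedom, so power = 0.78.

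**Step 2: right coding.**
- Mean effect = 0.6 × [p + (1 − p)k].
- Extra variance of change in the intervention arm, because the effect varies between participants = p(1 − p) × [0.6(1 − k)]².
- SD = √(0.6 + half the extra variance), averaging the two arms.

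| Other side gains | Mean effect | Extra variance | SD | Standardised effect | Power |
|---|---|---|---|---|---|
| nothing (k = 0) | 0.30 | 0.0900 | 0.803 | 0.374 | 0.26 |
| half (k = 0.5) | 0.45 | 0.0225 | 0.782 | 0.576 | 0.53 |
| 80% (k = 0.8) | 0.54 | 0.0036 | 0.776 | 0.696 | 0.69 |
| the same (k = 1) | 0.60 | 0 | 0.775 | 0.775 | 0.78 |

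Simulation of the same test gave 0.24–0.28, 0.52–0.53 and 0.68–0.71 for the first three rows, and essentially no loss for the fourth.

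**Step 3: how far the assumptions matter.**
- 23 evaluable per arm: paretic coding 0.73; right coding 0.24, 0.48, 0.64 and 0.73 for the four rows.
- Share paretic on the right of 0.4 or 0.6, k = 0, 26 per arm: about 0.185 or 0.355 against 0.78.
- Correlation 0.5, k = 0: 0.18 against 0.56. Correlation 0.8, k = 0: 0.36 against 0.92.
- Fallback ANCOVA, simulated at ρ = 0.7: about 0.84–0.85 for paretic coding against 0.28–0.30 (k = 0) and 0.58–0.60 (k = 0.5). With equal effects it is 0.82–0.84, almost no loss.

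The pattern is the same throughout: the loss is set by how unequal the two directions are, and it vanishes when they are equal.

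**The case against.** The strongest reply is that right and left are instructions to an assessor. The sentence on the final three trials fixes averaging over trials, and turning recorded values into analysis variables is commonly left to an analysis plan, which is not shown. That is fair, and an unseen plan may already recode. But the article names the conditions, assigns each a mean for analysis, and anchors the neighbouring measures to the affected side. A recode would therefore change what the article states, so the wording deserves correction either way.

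Three stronger readings are tempting and are not supported.
- *That the lateral measures have no clinical meaning.* Each is a reach distance compared between randomised groups. It estimates, without bias, the average effect over the enrolled mix of sides. It lacks a side-specific meaning, not all meaning.
- *That the trial cannot show whether weak-side reach improved.* Right reach, left reach and paretic side are all recorded, so weak-side reach can be derived for every participant with a recorded paretic side.
- *That power is lost regardless.* The loss needs a side-specific effect, and the documents give no evidence of one. Section 2.8.1 describes trunk, limb, balance, aerobic, sit-to-stand and side-walking exercises, with no stated targeting of the paretic side. The case where the other direction gains nothing is an extreme assumption.

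**Conclusion.** The point stands as a free improvement, not as an analysis error. As written, the two lateral measures average over paretic and non-paretic directions and do not directly estimate change toward the weak side. Under the planned group-by-time test and the assumed values, power falls from about 0.78 to between 0.26 and 0.69 when the other direction gains between nothing and 80% as much. With equal effects there is no material loss. The loss is measured against the more responsive direction; a mixed measure has more power than the less responsive direction taken alone.

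Effect size, correlation and split of sides are all assumed, since the documents give none of them for the MFRT. The MFRT is a secondary outcome. The primary outcomes (Trail Making Test and Timed Up and Go), the sample size and the validity of the between-group comparison are untouched.

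**What to change.** Leave the test procedure as it is. Add a sentence to section 2.10.2 defining the two lateral analysis variables as reach toward the paretic side and reach toward the non-paretic side, derived from the side recorded under section 2.4, and analysed in place of right and left. The same sentence should say how a participant without a single paretic side would be handled. The recode should be made before the multiple imputation in section 2.11, so that the imputation model works on the variables that will be analysed.

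The cost is wording only: no new data, visits or participants. Section 2.2 puts recruitment between February 2026 and March 2027, so the definition can be fixed before any outcome data are compared by group, which avoids a later choice between two codings. If an analysis plan already recodes, the article should be brought into line with it.
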